#### Self-Esteem Scale

The SES [9] is a short, ten-item questionnaire that evaluates global self-worth by questioning positive and negative feelings about the self. The origin of self-esteem seems to be composite and may be searched in early childhood, parental models, and context favoring personal development (e.g., parental concern, education, sports participation). The unidimensionality of the scale seems demonstrated, although all items are not weighted equally in the construct analysis [25]. Self-esteem appears an important issue in our study because its level conditions whether individuals will seek social support when they are confronted with unsolvable problems [26]. This attitude may impact the way they take into account the messages delivered during our intervention and how they will adapt their life strategies thereafter. Self-esteem has also proven to influence the level of hope, with persons with the higher self-esteem entertaining more hope [27].

Answers are quoted using 4-point Likert scales ranging from “strongly agree” to “strongly disagree.” We expect that a familial cancer predisposition might lower self-appraisal and that a more positive regard of it might contribute to an increase in SES score. The SES has been validated in French with different samples, including people with schizophrenia [28].

#### State and Trait Anxiety Inventory (STAI-A and STAI-B)

The STAI [11] is a questionnaire widely used to evaluate anxiety in such a way it cannot be confused with depressive syndrome. It comprises 40 items rated on a 4-point scale from “almost never” to “almost always.” The first 20 items evaluate anxiety as a state, corresponding to a labile/contextual aspect. The last 20 items estimate anxiety as a personality trait, independent of the environment. In our study, we expect, after our psychoeducational intervention, a larger change of state anxiety than of trait anxiety. Also, we assume that a reduction in anxiety will correlate with an increase in hope (HHI score). The STAI has been translated into French and validated by Schweitzer and Paulhan [29].

#### Ways of Coping Checklist

Coping is a wide concept. It can be defined as either a personality trait (“characteristic ways of responding to changes of any type in the environment” [30]) or a behavioral characteristic (“a conscious, intentional, goal-directed response, tailored to the specific demands of a stressor” [31]). The WCC [12, 13] has been translated into French in several versions: by Vitaliano (42 items) [32] and, based on this first translation, one by Schweizer and Paulhan (29 items) [29] and one by Bruchon-Schweitzer (27 items) [33]. We decided to use this last one [33], validated in 2010 in cancer patients by Cousson-Gélie et al. [34] despite a reduced set of 27 items. In the French 27-item version, the 2 main dimensions have been confirmed, characterizing either the focus on the problem (10 items) or the focus on emotions (9 items). A third dimension has been found, consisting in the search for social support (8 items) [33].

#### Perceived control (Internal, Powerful Others, and Chance Locus of Control *Scales*)

Perceived control synthesizes the equilibrium between actions launched by the individual and the feedback returned by the individual’s environment. Levenson’s Internal, Powerful Others, and Chance Locus of Control Scales (IPC) [14, 35, 36] is one of the most often used questionnaires to analyze how individuals try to control their destiny. Locus of control can be perceived either (1) within the self or (2) outside the self with two origins: fate/luck and “powerful others.” Depending on the locus, an individual’s cognition and behaviors vary. In young women exposed to a high familial cancer risk, the locus may appear to be outside the self (a *BRCA* mutation is like a twist of fate). Our intervention will try to teach how, with adapted behaviors (i.e., mainly changes in life habits), overall cancer risk can be halved, meaning that a part of the locus of control dwells, in fact, within the individual. A low level of perceived control has been proven to be related to psychological disorders such as depression [37] as well as a low HHI [22]. The 24-item IPC has been translated into French by Loas et al. [38].

#### Quality of life (WHOQOL questionnaire)

QoL is the subjective result of the many interactions between individuals (including health status) and their environment. Because it constitutes the focal point of all these interactions, we thought it might be of interest to check how our intervention could influence QoL over the long run. The WHOQOL questionnaire [17] has been preferred to other validated scales (e.g., European Organization for Research and Treatment of Cancer Quality of Life Questionnaire Core 30 for Cancer [EORTC QLQ-C30] [39], 36-item Short Form Health Survey [SF-36] [40]) because it does not focus on health-related QoL. The version used in our study corresponds to the WHOQOL-BREF (26 items). This version was derived from the 100-item WHOQOL and showed similar properties. The authors suggested that this short version could advantageously replace the long version in trials and surveys investigating QoL [17]. It contains four main dimensions: physical health, psychological health, social relationships, and environment. These dimensions have been confirmed in the French translation by Leplège et al. [41].

### Methodology

#### Sample size

Sample size has been determined by taking into account two factors: first, the need for small groups for the sessions to be efficient (i.e., letting all participants get involved in the exercises and have time to share their emotions or opinions), and second, the need for the trial to have sufficient power to evidence differences. Our target is to objectivize differences between groups of at least 1 SD of the differential variation in the HHI questionnaire score between inclusion and 6 months. This hypothesis is compatible with the results published by Herth et al. [16], who found that, after a psychosocial intervention in cancer patients, the improvement to the global HHI score equaled 9 points with an SD of 9.9. An expected 1-SD difference may be questioned, however: Herth’s population corresponded to cancer patients aged between 20 and 80 years. Our population is healthy, evidently much younger, and includes only females. One of our expectations is that the study outcome invalidates or confirms if this reference was relevant; if not, this will help further studies to build a better-fitting design. With this 1-SD hypothesis, a one-sided α-risk equal to 0.05, and 80 % power (β = 0.20), at least 12 participants per group will have to be accrued. Considering that some participants may refuse at the last moment to come to the session, two more participants will be accrued per arm. Overall, 28 participants need to be included.

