**Methods/design:**

The BRACAVENIR study consists of a prospective, randomized superiority phase II trial with a wait list control group. Participants are childless young female counselees (aged 18–30 years) seen at the oncogenetics department of the Centre Jean Perrin and belonging to HBOC families either with or without *BRCA* mutations. They will be invited to attend a weekend group session at a spa resort and to participate in short expert conferences and focus group activities (group sharing, Moreno role game) supervised by a psychotherapist. Two sessions separated by a 6-month delay (wait list) will enable us to evaluate the intervention’s effect by comparing questionnaire scores between the 6-month time points. The main endpoint is an increase of the Herth Hope Index by at least 1 SD. Secondary endpoints are self-esteem, anxiety trait, anxiety state, coping, and quality of life. With a one-sided α = 0.05 and β = 0.20, 12 participants will be needed by group, plus an additional 2 in anticipation of dropouts. Participants will be randomized 1:1 to the first or the second session so that the groups will be comparable.

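### Twelve women per group give about 77% power for a 1-SD difference with the planned t test, not 80%; the two extra women per arm are needed to reach 80% and do not protect it

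*Protocol article*

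**What the plan says.** The Sample size section sets the target as "differences between groups of at least 1 SD of the differential variation in the HHI questionnaire score between inclusion and 6 months". The error rates are "a one-sided α-risk equal to 0.05, and 80 % power (β = 0.20"), and the conclusion is that "at least 12 participants per group will have to be accrued". Two women per arm are then added because "some participants may refuse at the last moment to come to the session", for a total of 28.

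The Abstract gives the same split: "12 participants will be needed by group, plus an additional 2 in anticipation of dropouts". The Discussion returns to it, saying that the sample was enlarged slightly so that withdrawals would not erode a power of 80% that it already regards as limited.

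The Data analysis section names the primary test: Student's t test on each woman's HHI change from inclusion to 6 months, with the Mann-Whitney test as fallback. The Randomization section fixes 1:1 allocation.

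In support of 1 SD, the Sample size section cites a study in cancer patients in which "the improvement to the global HHI score equaled 9 points with an SD of 9.9", and calls the hypothesis compatible with it. It then adds: "An expected 1-SD difference may be questioned, however".

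**The concern.** Effect size, alpha, sidedness, power, allocation and test are all stated in the article, so the number per group can be checked without the statistical analysis plan. The article presents 12 as the minimum that delivers 80%, and the next two women per arm as insurance. If 12 falls short and the planned test needs 14, there is no insurance: losing the two women per arm that the plan allows for takes the trial below the power it claims to have protected.

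What is at stake is how the trial describes its own sensitivity. At 12 per group the chance of missing a true 1-SD difference is about 23% (100 − 76.7), against the stated 20%. Readers who weigh a null result should have the correct figure.

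**Working it through.** **Inputs (all from the protocol article).** Standardised difference d = 1, one-sided alpha 0.05 and power 0.80 (Sample size); 1:1 allocation (Randomization); two-sample Student t test on change scores (Data analysis).

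**Step 1. The plan's own figure.** The normal approximation for two means is n per group = 2(z₀.₉₅ + z₀.₈₀)² / d² = 2(1.645 + 0.842)² / 1² = 12.37.

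The stated 12 is this value rounded to the nearest integer. A minimum sample size is rounded up, which gives 13. The two-sided version gives 16, so the article did use the one-sided formula.

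**Step 2. Power at 12 by the same formula.** Power = Φ(d√(n/2) − 1.645) = Φ(2.449 − 1.645) = Φ(0.804) = 78.9%. At 13 per group it is 81.7%. So 12 falls about 1 point short even by the more favourable formula.

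**Step 3. Power of the planned t test.** The exact calculation uses the noncentral t distribution with 2n − 2 degrees of freedom and noncentrality d√(n/2). Power is the probability of exceeding the one-sided 5% critical value.

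| n per group | df | noncentrality at d = 1 | power |
|---|---|---|---|
| 12 | 22 | √6 = 2.449 | 76.7% |
| 13 | 24 | √6.5 = 2.550 | 79.7% |
| 14 | 26 | √7 = 2.646 | 82.4% |

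The smallest n that reaches 80% is 14. Since 14 − 12 = 2, the gap equals the whole dropout allowance.

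**Step 4. Detectable difference.** Solving the same equation for d at 80% power gives 1.05 SD with 12 analysed per group and 0.97 SD with 14.

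**Step 5. Sensitivity only.** The cited figures give 9 / 9.9 = 0.909. If that ratio is taken as the between-group effect in SDs of the change, which the text does not confirm, the t test has 69.6% power at 12 per group and 75.7% at 14. It would need 16 per group for 80% (power 80.7%).

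**The case against.** The best defence is that this is a rounding matter. The standard formula gives 12.37, and 12 per group yields 78.9%. The article says at least 12 and then enrols 14, which gives 82.4% if all are analysed; with one loss per arm the figure is 79.7%, which most readers would call 80%. Small session groups are also named as the first factor behind the sample size, so power was never its only driver. All of this stands, and it limits the size of the point. It does not rescue the sentence that 12 suffices, or the description of the other two as spare.

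A reader might infer more than the documents support:

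- **That the true power is 70%.** This needs 0.91 SD as the design effect. The article powers for 1 SD and says openly that this may be questioned. It does not say whether the cited 9 points are a between-group difference or a change within one group, or whether 9.9 is the SD of the change. The 70% is a sensitivity figure, not a contradiction of the stated 80%.
- **That women who miss the session will dilute the effect.** Home questionnaires make it possible to follow them, but the article does not say how they are analysed. That can properly be left to the statistical analysis plan. Any figure would also need assumed numbers of non-attenders and an assumed effect in them.
- **That the Mann-Whitney fallback lowers power further.** It is used only if normality or equal variance fails, and the article describes no such setting in which its power could be calculated.
- **That the later phase III trial will be too small.** The Discussion says that this trial is to estimate effect sizes for that purpose, so the planning would rest on those estimates and not on the 12 per group used here.

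**Conclusion.** The statement that 12 per group gives 80% power is wrong for the article's own inputs. The figure is 78.9% by the normal approximation and 76.7% for the planned t test, a shortfall of about 1 and 3 percentage points respectively. The t test needs 14 per group, so the two extra women per arm are required to reach 80% and cannot also protect it. The design as enrolled is adequate for its target: 28 women, all analysed, give 82.4%.

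Severity is minor to moderate. The result assumes normally distributed change scores with equal variance in the two groups, which are the conditions under which the article would use the t test, and a true difference of exactly 1 SD.

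**What to change.** Keep 28 women and correct the wording in the Abstract, the Sample size section and the Discussion, for example:

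> Fourteen women analysed per arm give 82% power for a 1-SD difference in HHI change (one-sided alpha 0.05, Student t test). If losses leave 12 per arm, power is 77%, and the difference detectable with 80% power is 1.05 SD.

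The statement that 12 per group are sufficient, and the description of the other two as a reserve that preserves 80%, should be removed.

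Optionally, add one sentence labelled as sensitivity: if the cited ratio 9 / 9.9 = 0.91 is assumed to be the between-group effect in SDs of the change, power is 76% with 14 and 70% with 12 per arm. It should not replace 1 SD as the design effect, because the text does not establish that it is the same quantity.

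The cost is wording only: no extra participants, and no change to the sessions, the test or the schedule. The stated power becomes conditional on retention, which makes complete 6-month questionnaires matter more.

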#### Data management

Data will be collected using an electronic case report form (eCRF). Capture System software (Clinsight, Cenon, France) will be used to allow participants to complete their questionnaires by Internet from home. They will be enabled to input data without the possibility of consulting their previous answers (questionnaires at inclusion or at sessions). This blinding is important to prevent both a back-correction of previous answers and also to limit the risk of a direct copy for participants who would avoid recanting. Data will be monitored according to the specifications defined for this kind of study; in particular, special attention will be paid to limit the amount of missing data. Two kinds of control will be performed using the software. First, the eCRF will automatically signal if a question is not answered. However, the participant keeps the right to confirm the missing item. Second, if an entire questionnaire is not completed, because this might be an omission, a message will be sent by the data manager through the mailing device of the software to ask the participant to complete the form or to confirm that she did not forget to fill the questionnaire but intentionally left it blank.

#### Data analysis

A statistical analysis plan will be written prior to conducting any outcome analysis, excluding queries to manage data. The statistical analysis will start after the database is locked. This will be done in two steps when the 6-month and then the 12-month questionnaires are collected.

Data analysis will begin with a description of population characteristics (age, known *BRCA* mutation, socioeconomic and educational categories). The balance of these characteristics will be checked by allocation group. Missing data will be analyzed by group, by type of questionnaire, and by time (inclusion, sessions, 6 and 12 months). Further description will present the longitudinal analysis of questionnaire scores over the course of 1 year. Differences related to socioeducational and socioeconomic categorical data and scores at inclusion will be analyzed using one-way analysis of variance (ANOVA) or Kruskal-Wallis H test. Overall convergent/divergent analysis between scores, independently of groups and times, will be verified by correlation analysis (Pearson’s or Spearman’s correlation if distributions are abnormal). A correspondences analysis will present the global description of the results and the relationships between questionnaire dimensions.

The main endpoint will be tested between allocation groups using individual HHI score variations (change at 6 months from time of inclusion) by Student’s *t* test or Mann-Whitney *U* test if normality/homoscedasticity is not achieved. All scores by group will be analyzed longitudinally using two-way ANOVA (mixed model) with either raw scores or their variation from baseline.

The statistical analysis will be performed using SEM software [42] and R version 3.0.1 software. The SPIRIT checklist, describing correspondances between the protocol and standard issues addressed in clinical trial, is provided as Additional file 1.

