Another discussed subject was the “good” time to start evaluating the intervention. The baseline measure was initially placed at inclusion. Because the accrual period will last about 2 months, however, the 6-month delay would not be respected for participants included early. We thus decided to shift the questionnaire self-completion at a fixed time point 2 weeks before the first session for everybody. Meanwhile, as the provision of socioeconomic data at inclusion might be a good opportunity to teach the participants how to use our dedicated website, we decided to reserve a moment after obtaining the consent signature to explain how to enter the site and complete the forms. The evolution of the other estimates and the cross-correlation analysis of questionnaire dimensions will help us to determine if another aspect should be used instead of the focus on “hope” to improve, with better efficacy, the overall QoL of our young women.

Finally, we as yet have no idea how our proposal will be perceived by our young asymptomatic women. The rate of refusal and the reasons by which they will justify their not entering the study will be analyzed and will help us develop better prevention strategies for the youngest counselees. One of the purposes of this phase II trial is to verify the feasibility and acceptability of the intervention to participants, evaluate its effect size on the various scales, and prepare a larger national phase III trial based on a more solid hypothesis. The acceptability is of major importance, and a better definition of the young population that we target may need some adjustments. In particular, the birth of one child does not eliminate worries regarding new procreation projects; perhaps it even increases them as questions about the long-term security of the child (Will I live long enough to ensure his future?) are suddenly raised by his arrival. So, the inclusion criteria of our pilot study will probably need to be widened in a further trial to include young women facing more concretely not only the transmission dilemma of their mutation but also familial existential issues.

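### Correlations between questionnaire scores are planned on data pooled over arms and occasions, which mixes repeated records from the same women and would overstate the precision of any p-value or confidence interval

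*Protocol article*

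**What the plan says.** The protocol article, section Data analysis, describes the step in one sentence: "Overall convergent/divergent analysis between scores, independently of groups and times, will be verified by correlation analysis". The coefficient is named in brackets: "Pearson’s or Spearman’s correlation if distributions are abnormal". No repeated-measures form of either coefficient is mentioned. A mixed model is named in the same section, but only for the course of scores by group.

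Table 1 (section Study design) marks the psychosocial questionnaires at five occasions: baseline, session 1, the main outcome time, session 2 and the final assessment. It does not say whether women who are not attending a session also answer at that time. The number of women is fixed under Sample size: "Overall, 28 participants need to be included".

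The Discussion gives the result a use. Together with the evolution of the other estimates, the "cross-correlation analysis of questionnaire dimensions will help us to determine if another aspect should be used instead" of hope. The following paragraph of the Discussion gives as one purpose of the trial to "prepare a larger national phase III trial based on a more solid hypothesis".

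**The concern.** Ordinary Pearson and Spearman inference assumes that each row is an independent subject. Here the independent unit is the woman, and stacking her repeated questionnaires multiplies rows without adding women.

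There are two consequences. First, the coefficient has no single meaning. Whether women with high self-esteem have more hope is a question between women. Whether a woman whose anxiety falls gains hope is a question about change. The article raises both, the first under Self-Esteem Scale and the second under State and Trait Anxiety Inventory, and a pooled coefficient isolates neither. If two scales both move after the session, the pooled data will also show them as related even if they are otherwise unconnected. Second, any p-value or interval based on the row count will look more certain than it is.

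At stake is the reading of the psychological model, and one of the inputs to reconsidering hope as the focus of the intervention.

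**Working it through.** The plan states no figure for this step, so there is none to reproduce.

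**1. Rows.** Women: 2 × (12 + 2) = 28, from Sample size. Records per woman (m), from Table 1: 5 if all women answer at every marked occasion, 4 if only attendees answer at a session, 3 if session forms are left out. Rows: 28 × 5 = 140, 28 × 4 = 112, 28 × 3 = 84.

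**2. What the pooled coefficient estimates.** With equal ICC on both scales and no shift, pooled r = ICC × (between-woman correlation) + (1 − ICC) × (within-woman correlation). It is a weighted blend whose weights depend on an unstated ICC.

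**3. Effect of a common shift (illustration, assumed).** Take two unrelated scales with SD 1, each rising by 1 SD after the session and staying there. With three occasions and equal arms, the first group is post-session at 2 of 3 records and the second at 1 of 3, so half of all records are post-session. The shift adds 0.5 × 0.5 × 1² = 0.25 to each variance and 0.25 to the covariance. Pooled r = 0.25 / (1 + 0.25) = 0.20, although the scales are otherwise unrelated. This does not depend on any test being reported.

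**4. Precision.** When the true correlation is zero, the variance of a pooled correlation is inflated by DE = 1 + (m − 1) × ICC_x × ICC_y. The correct interval is √DE times wider. The article gives no ICC, so 0.3 to 0.9 is assumed, equal on both scales. Example, m = 5 and ICC 0.7: DE = 1 + 4 × 0.49 = 2.96, √2.96 = 1.72, effective n = 140 / 2.96 ≈ 47.

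Type I error and coverage come from simulation (20,000 runs, 28 women, random-intercept scores with zero cross-correlation and no shift, Fisher-z test treating all rows as independent):

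| m | ICC | DE | interval factor √DE | type I error of nominal 5% test | coverage of nominal 95% CI |
|---|---|---|---|---|---|
| 3 | 0.3 | 1.18 | 1.09 | 7% | 93% |
| 3 | 0.5 | 1.50 | 1.22 | 11% | 89% |
| 3 | 0.7 | 1.98 | 1.41 | 17% | 83% |
| 3 | 0.9 | 2.62 | 1.62 | 24% | 77% |
| 5 | 0.3 | 1.36 | 1.17 | 9% | 91% |
| 5 | 0.5 | 2.00 | 1.41 | 17% | 83% |
| 5 | 0.7 | 2.96 | 1.72 | 26% | 74% |
| 5 | 0.9 | 4.24 | 2.06 | 35% | 65% |

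Replacing the rows by one mean per woman (n = 28) brought the simulated type I error back to about 5%.

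**5. Unequal stability.** If one scale is stable (0.8) and the other labile (0.3), the product is 0.24. At m = 3, DE = 1.48 and the factor is 1.22; at m = 5, DE = 1.96 and the factor is 1.40.

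**6. In practical terms.** Interval: tanh(atanh r ± 1.96/√(n − 3)). For r = 0.40, counting 140 rows gives 0.25 to 0.53; counting 28 women gives 0.03 to 0.67. The smallest |r| reaching p < 0.05 is tanh(1.96/√137) = 0.17 with 140 rows, 0.21 with 84 rows and 0.37 with 28 women.

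**The case against.** The case on the other side has several parts.

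- **No inference is promised.** The article states no p-value, interval or threshold for these correlations, and the step stands beside a correspondence analysis meant as a global description. This stands: the loss of precision is conditional on such figures being reported. The blending in steps 2 and 3 is not conditional, because it affects the coefficient itself.
- **A statistical analysis plan is still to come.** Handling of repeated records could be set there. This stands only in part. The article does not leave the data set open: it says that groups and times are pooled and names the ordinary coefficients. An analysis plan that follows the text would inherit the problem.
- **The size depends on assumptions.** A reader might infer that intervals would be far too narrow. The documents do not support that in general, since no ICC is given and five records is a maximum. At ICC 0.3 with three records the factor is only 1.09. The article calls self-esteem and trait anxiety stable and assumes expectations are stable over six months without intervention, which points away from the low end. It also calls state anxiety and expectations labile.
- **Zero correlation is not the expected truth.** The article expects these constructs to correlate, so false rejection of zero is of limited interest. This is fair, but under-coverage is similar for non-zero correlations: with a true correlation of 0.5, five records and ICC 0.7, simulated coverage was also 74%.
- **The use is softer than it may look.** A reader might infer that these correlations choose the phase III target. The Discussion makes them one of two inputs that help reconsider the focus on hope. The phase III sentence is in the next paragraph and speaks of feasibility, acceptability and effect size. The Discussion also refers to questionnaire dimensions, a term that Data analysis attaches to the correspondence analysis. The pooled step is the only correlation analysis of scores in that section, so the link is likely but not certain.

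**Conclusion.** The point holds as a flaw in a stated secondary method. As written, about 3 to 5 non-independent rows from each of 28 women enter ordinary correlation coefficients, and the result blends between-woman association, within-woman change and any common post-session shift. If p-values or intervals are attached, they will overstate precision by an amount that ranges from slight to large over the assumed ICCs and record counts. The sizes rest on a random-intercept model without shift.

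The primary comparison of HHI change between arms, the sample size and the efficacy conclusion are untouched. The documents do not support saying that the plan's intervals are wrong, since none are promised, or that the next trial's target will be chosen from these correlations. The change is worth making because the Discussion gives the result a role and the correction needs no new data.

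**What to change.** In the statistical analysis plan, replace the pooled analysis with the following:

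- **Convergent and divergent correlations:** use the baseline questionnaires only, completed before the first session, with one row per woman (n = 28, or 24 if all four spare places are lost).
- **Associations of change:** correlate individual baseline-to-6-month changes, adjusted for arm, so that a shift common to the treated group is not read as convergence.
- **If all occasions are used:** use repeated-measures correlation for the within-woman association, or a bivariate mixed model that separates the between-woman and within-woman parts. Remove the arm-by-occasion means first. Take any confidence interval from a bootstrap that resamples women, not rows.
- **Reporting:** state which of the two associations each coefficient describes, and label the analysis exploratory.

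The cost is some wording, slightly more analysis work and wider intervals. Baseline-only correlations give up information when scores are labile: at ICC 0.3 with five records the pooled data would be worth about 140 / 1.36 ≈ 103 independent rows, against 28. The repeated-measures option recovers some of this for within-woman change. No extra data collection is needed, and the primary analysis stays as it is.

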### Randomization

Participants will be randomized 1:1 to the first or second session (intersession delay = 6 months) using a minimization technique and stratified according to the existence or absence of a familial *BRCA* mutation. We assumed that this characteristic might induce variations in coping and expectations and thus alter the impact of the psychoeducational intervention if the studied population were not balanced with regard to this characteristic.

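### The primary test on raw HHI change is valid, but one prespecified ANCOVA on baseline HHI and familial BRCA status would usually give more power at no extra cost

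*Protocol article*

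**What the plan says.** The Data analysis section of the protocol article states the primary test: "The main endpoint will be tested between allocation groups using individual HHI score variations", meaning change from inclusion to 6 months. It uses Student's t, or the Mann-Whitney U "test if normality/homoscedasticity is not achieved". It names no covariate for this test.

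The same section adds a longitudinal model: "All scores by group will be analyzed longitudinally using two-way ANOVA (mixed model) with either raw scores or their variation from baseline". BRCA status is not named there either.

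The Randomization section describes 1:1 minimisation, "stratified according to the existence or absence of a familial" BRCA mutation. The reason given is: "We assumed that this characteristic might induce variations in coping and expectations". Expectations are the construct that the article measures with the HHI, its primary endpoint.

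The Sample size section targets "differences between groups of at least 1 SD of the differential variation in the HHI questionnaire score between inclusion and 6 months", with "a one-sided α-risk equal to 0.05" and 80% power. The result is 12 per group, raised to 14 to allow for dropout.

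**The concern.** A change score removes baseline by subtracting it in full. Unless baseline and follow-up are very highly correlated, that over-corrects and leaves more residual noise than letting the data estimate the baseline coefficient. With 24 to 28 women, the difference can decide whether the trial reaches its stated power.

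The plan also balances the arms on a factor it considers potentially influential and then leaves that factor out of the test. If the factor is prognostic, the standard error is larger than it needs to be and the test is conservative.

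Finally, the data choose the primary test. The trial was sized on a mean difference, but a failed check would replace it with a rank comparison. Mann-Whitney is not a remedy for unequal variances, which is one of the two conditions that trigger it.

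**Working it through.** **Inputs from the Sample size section.** Effect 1 SD of the HHI change, one-sided α 0.05, power 80%, 12 per arm (14 with the dropout allowance).

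**Assumptions.** The article gives no r, so a range is shown. SDs at baseline and 6 months are taken as equal.

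**Step 1: the plan's own figure.** The normal approximation gives n = 2(z₀.₉₅ + z₀.₈₀)²/1² = 2(1.645 + 0.842)² ≈ 12.37 per arm. The stated 12 is therefore reproduced to within rounding (13 if rounded up). The noncentral t is stricter:
- 12 per arm: noncentrality 1/√(2/12) = 2.45, 22 df, power 76.7%.
- 13 per arm: 79.7%.
- 14 per arm: 82.4%. This is the first size to reach 80%.

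**Step 2: adjusting for baseline.** With common SD s, the variance of a change is 2s²(1 − r), and the ANCOVA residual variance is s²(1 − r²). Their ratio, ANCOVA to change, is (1 + r)/2. One covariate costs one df and, on average, inflates the variance by 1 + 1/(2n − 4), which is 1.05 at n = 12. The noncentrality is then 1/√(2 × ratio × 1.05/12).

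| r | Ratio | Noncentrality, 12/arm | Power, 12/arm | Power, 14/arm | n/arm for 80% |
|---|---|---|---|---|---|
| change score t | 1 | 2.45 | 76.7% | 82.4% | 14 |
| 0.3 | 0.65 | 2.96 | 88.9% | 93.1% | 10 |
| 0.5 | 0.75 | 2.76 | 84.7% | 89.7% | 11 |
| 0.7 | 0.85 | 2.59 | 80.6% | 86.2% | 12 |
| 0.9 | 0.95 | 2.45 | 76.7% | 82.7% | 14 |

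**Step 3: adding BRCA.** Simulation at 12 per arm, BRCA balanced between arms:
- *BRCA not prognostic:* ANCOVA with baseline and BRCA has about 89%, 85%, 80% and 76% power at r = 0.3, 0.5, 0.7 and 0.9. Adding BRCA therefore costs about 1 point or less. Without that balance, the formula with two covariates puts the cost at 1.5 to 2 points; the minimisation is there to prevent this.
- *BRCA shifts the change by 0.5 SD (assumed, r = 0.5):* t test 74%, ANCOVA with both covariates 84%. The t test's one-sided type I error is 4.4%.
- *BRCA shifts it by 1 SD:* 69% against 85%. The t test's type I error falls to 2.8%.

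In the last two cases the treatment effect stays at 1 SD of the change within BRCA strata.

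**Step 4: the switching rule.** The article names no check or threshold. Assuming Shapiro and Levene tests at 5%, with 12 per arm:
- Power is within 1 point of the plain t test.
- Type I error is 4.7% with normal data, 5.4% with skewed residuals and 5.0% with the residual SD doubled in one arm.
- With ceiling-type skew and a 2:1 SD ratio together, rejection at equal means is 13% to 15% if the intervention arm has the larger SD (Welch's t about 8%), and about 2% if the control arm has it.

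**The case against.** The strongest defence is that the planned test is not wrong. Randomisation protects an unadjusted comparison of changes from bias, and the trial was sized on the SD of the change, so sizing and test agree. The article also says a statistical analysis plan will be written before any outcome analysis, and assumption-check details could be set there. Validity and coherence stand. The deferral answers less, because the article has already fixed the form of the primary test and its switching rule.

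Three stronger readings are tempting but not supported:
- *The plan ignores baseline.* It does not. A change score uses baseline with a fixed coefficient of 1. The issue is efficiency, and it fades as r approaches 0.9.
- *Power is certainly being wasted on BRCA.* The article says only that BRCA might matter for expectations. An equal effect on HHI at both times cancels in the change score. The t test loses from the omission only if BRCA predicts the change itself.
- *The switching rule inflates type I error to 14% or so.* That needs skew, a 2:1 SD ratio and the larger SD in the intervention arm, all together. Reversing the arms makes the rule conservative, and Welch's t also exceeds 5% in the inflating case. In ordinary settings the error rate is near 5%.

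The trial is also a phase II pilot, intended partly to estimate effect sizes for a phase III. That lowers the stakes of a single p-value, but it strengthens the case for one adjusted mean difference with an interval.

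**Conclusion.** The concern holds as an improvement in efficiency and clarity; it is not an error that invalidates the trial. At 12 per arm, the planned test has about 77% power for a 1-SD effect. Baseline adjustment adds roughly 12 points at r = 0.3, 8 at r = 0.5 and 3 to 4 at r = 0.7, and nothing near r = 0.9. These gains assume equal SDs at the two times and ordinary model-based standard errors. Including BRCA protects against a conservative test if it is prognostic given baseline, and costs about 1 point or less if it is not, provided the minimisation balances it.

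The switching rule is the smaller part. The objection to it is mainly that the hypothesis tested, and so the effect reported, depends on a preliminary check. Its type I error departs materially from 5% in the simulations only when skew and unequal variance occur together, and then in either direction.

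**What to change.** In the statistical analysis plan, prespecify one primary analysis: ANCOVA of the 6-month HHI total on arm, baseline HHI and familial BRCA mutation (yes/no), one-sided α 0.05, reported as an adjusted mean difference with a two-sided 90% confidence interval. Drop the preliminary-test switch. Keep Welch's t and Mann-Whitney on the change score as labelled sensitivity analyses.

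Use ordinary model-based standard errors. A heteroscedasticity-robust HC3 version is an obvious addition, but it is conservative at this size: simulated power at 12 per arm is about 81% at r = 0.5, 74% to 76% at r = 0.7 and 71% at r = 0.9, so the gain disappears from about r = 0.7.

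The cost is a change of wording and two degrees of freedom. Baseline HHI and BRCA status are already collected, and no additional participants are needed.
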